### Study setting and sampling

The study will be carried out in public primary and secondary/junior high schools in Tanzania, Uganda, and Ghana. A multi-stage sampling procedure was applied to ensure a sample of schools that can be considered representative for each country in terms of geographical, socio-economic, and political aspects. At each stage, the respective sampling units (zones, regions, districts) were weighed by their number of schools according to probability-proportional-to-size sampling. First, three administrative zones were randomly selected in each country. Next, one region in each of the selected zones in each country was randomly selected. In the next step, one district in each of the chosen regions in each country was randomly selected. The selected zones, regions and districts per country are displayed in Table 1.

**Table 1 Tab1:** Selected zones, regions and districts per country

Country	Zone	Region	District
Tanzania	Eastern/Coastal	Lindi	Kilwa District Council
	Lakes	Mwanza	Mwanza City Council
	Southern Highlands	Iringa	Iringa District Council
Uganda	Central	Buganda	Kayunga District
	Western	Toro	Kasese District
	Northern	Acholi	Pader District
Ghana	Southern	Central	Mfantseman Municipality
	Middle	Bono East	Techiman Municipality
	Northern	North East	Bunkpurugu District

*Notes:* Three zones each were randomly selected from the six zones in Tanzania (Northern, Eastern/Coastal, Central, Lakes, Southern Highlands, Zanzibar) and from the four zones in Uganda (Central, Western, Eastern, Northern). As a geographical division into three belts (Southern, Middle, Northern) is common in Ghana, each belt was included at this sampling stage. In Uganda, the region Buganda is equivalent to the Central zone

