#### Schools

In each of the selected districts, schools meeting the following criteria will be eligible for inclusion into the study: 1. Public, day-care and mixed-gender primary and secondary/junior high schools. 2. At least 40 students in the selected class/stream (class 3 in primary and form 1 in secondary/junior high school). In case a selected school has less than 40 students in a class or stream, it will be combined with a neighboring public school (within 15 km) to a school cluster and 20 students from each school will be selected. 3. At least 15 and no more than 50 teachers at a school. In case of less than 15 teachers, a school cluster with a neighboring school (within 15 km) will be formed and all teachers officially working at these schools will be included. The upper limit of 50 teachers is due to practical difficulties related to providing the intervention to a higher number of potential participants. Official lists of available schools will be obtained from the relevant authorities and schools will be stratified based on school type (primary vs. secondary/junior high) and whether the school is in an urban or rural setting. The latter will be determined using the database Africapolis (www.africapolis.org), which defines an agglomeration as urban if it constitutes a continuously built-up area with less than 200 m between buildings and its population exceeds 10.000. In the case of entirely urban districts, e.g., Mwanza in Tanzania, existing official classification on the ward level will be used. After listing the stratified schools in each district in alphabetical order, four primary (two urban and two rural) and four secondary/junior high schools (two urban and two rural) will be randomly selected in each of the three districts per country, implying a total of 72 schools (24 per country). The stratified randomization based on school type and urban/rural location results in 36 sites or school pairs, in which one school will be randomly allocated to the intervention group and one school to the control group (see Fig. 3). All random selections of country zones, regions, districts, and schools as well as the allocation of schools to the two study conditions are performed by an independent researcher neither belonging to the core research nor the data collection teams.

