### Data analyses

Baseline assessment data will be used to provide information about the prevalence of maltreatment and violence in different settings as well as children’s mental health and well-being. Longitudinal analysis will be carried out based on the groups as randomized (intention to treat). As drop-outs and missing data at follow-up assessment are likely given the longitudinal study design, we aim to apply full information maximum likelihood estimation to obtain unbiased parameter estimates. In our main analyses, we will investigate the effect of the intervention on the primary and secondary outcome measures in comparison to the control group. Due to the naturally nested data structure, we will apply multilevel analyses. Latent growth modeling or cross-lagged path models will be used to estimate the directional influence of violence by teachers on primary and secondary outcome variables over time. Results will be presented including appropriate effects sizes and with a measure of precision (95% confidence intervals). Effect size η^2^ ≥ 0.01, η^2^ ≥ 0.06 and η^2^ ≥ 0.14 will be considered to represent a small, moderate, and large effect, respectively [76].

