Previous trials of *ICC-T* have provided initial evidence for its feasibility and effectiveness at primary and secondary schools in Tanzania [3, 42] and at secondary schools in Uganda [4]. Like those studies, the current study will adopt a two-arm cluster randomized controlled trial design. However, it will extend the previous trials by including a larger number of clusters and a longer follow-up period of 18 months and by considering an additional educational setting (primary schools in Uganda) and cultural context (Ghana). In so doing, the study will provide a particularly strong test of the effectiveness of ICC-T and its generalizability across educational systems, countries, and cultures. Moreover, the longitudinal and experimental design including the controlled manipulation of violence by teachers through ICC-T will yield insights into temporal and causal associations between children’s exposure to violence and their mental health, psychosocial, cognitive, and academic functioning. The use of nationally representative samples of students and teachers in each country will inform about prevalence rates of violence in the school setting. To quantify students’ exposure to violence, we will not only rely on teachers’ reports, which may be biased in the direction of the intervention effect, but also on students’ self-reported exposure to violence, which can be considered a more conservative test of the intervention effect. The use of structured interview assessment and standardized cognitive and academic performance tests are likely to strengthen the validity of findings by reducing reporting and common-method bias.

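### The samples are called nationally representative, but three districts per country, equal stratum quotas and narrow school eligibility do not support that description or an unqualified national prevalence

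*Protocol article*

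**What the plan says.** The strongest claim is in the Discussion: "The use of nationally representative samples of students and teachers in each country will inform about prevalence rates of violence in the school setting". Study setting and sampling is more cautious and speaks of schools only: "a sample of schools that can be considered representative for each country in terms of geographical, socio-economic, and political aspects". Data analyses gives the descriptive use: "Baseline assessment data will be used to provide information about the prevalence of maltreatment and violence in different settings".

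The design is set out in Study setting and sampling, Schools, and Participants:

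- **Upper stages.** The top stage reads "First, three administrative zones were randomly selected in each country". A single region was then drawn per zone, and below that "one district in each of the chosen regions in each country was randomly selected". Selection is with probability proportional to size (PPS), size being the number of schools. The note to Table 1 adds that Tanzania has six zones and Uganda four, and that in Ghana all three belts were included.
- **Schools.** The take per district is fixed: "four primary (two urban and two rural) and four secondary/junior high schools (two urban and two rural) will be randomly selected in each". This makes eight schools from every district.
- **Eligibility.** Public, day, mixed-gender schools with 15 to 50 teachers. Schools that fall short on teachers, or have fewer than 40 students in the class, are merged with a neighbour within 15 km. Schools above 50 teachers are excluded for practical reasons.
- **Individuals.** Forty students per school, from the third primary year or the first secondary/junior high year, and all teachers.

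**The concern.** A sample that is nationally representative of students and teachers should cover the national population of each, with known selection probabilities that the estimates reflect, and with enough first-stage units to show how far the country figure could be off. The stated design falls short on coverage and on the number of first-stage units. Its stratum quotas and fixed student take also mean that students do not have equal chances of selection.

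This matters for what the trial can say about prevalence. The Background names reliance on small, non-representative samples as a major weakness of existing prevalence studies, and the Discussion implies that this trial does better. The limitations in the Discussion do not mention the sampling, and the results are addressed to governments and policy makers. A reader could take a figure from three districts as a national one.

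**Working it through.** **1. The plan's own counts.** 3 countries × 3 districts × 8 schools = 72 schools, 24 per country. 72 × 40 = 2880 students, or 24 × 40 = 960 per country. 72 × 20 = 1440 teachers. All agree with the article.

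**2. Does PPS selection make the samples self-weighting?** PPS by number of schools down to the district, followed by a fixed number of schools per district, would give schools roughly equal chances. Three features break this.
- The eight schools are split 2 + 2 + 2 + 2 by location and school type, so a school's chance depends on how many schools are in its stratum.
- Forty students are taken whatever the size of the grade, so a student in a large grade has a lower chance. This does not apply to teachers, who are all taken.
- In Ghana all belts are included, and each supplies eight schools whatever its size.

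**3. Bias if a country figure were pooled unweighted.** Let W be the true rural share and P_r, P_u the rural and urban prevalences. The unweighted figure is 0.5·P_r + 0.5·P_u and the target is W·P_r + (1 − W)·P_u, so

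bias = (0.5 − W) × (P_r − P_u).

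The article gives neither W nor the gap, so these are assumptions:

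| True rural share | Gap 0 | Gap 10 points | Gap 20 points |
|---|---|---|---|
| 50% | 0 | 0 | 0 |
| 60% | 0 | 1.0 | 2.0 |
| 70% | 0 | 2.0 | 4.0 |
| 80% | 0 | 3.0 | 6.0 |
| 90% | 0 | 4.0 | 8.0 |

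Entries are absolute percentage points; for example (0.5 − 0.9) × 20 = −8. The school-type quota has the same form, and the two biases could add or offset.

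**4. Precision of a country figure.** From the article: 960 students, 24 schools, 3 districts, and a school intraclass correlation of 0.05 for student-reported violence (given in Participants for the power calculation and borrowed here). Assumed: prevalence p = 0.70 and district intraclass correlation ρ_d of 0.01 to 0.05.

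Variance = p(1 − p) × [ρ_d/3 + 0.05/24 + (1 − 0.05 − ρ_d)/960].

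- Simple random sample: 1.96 × √(0.21/960) = ±2.9 points.
- School clustering only (ρ_d = 0): 0.21 × (0.002083 + 0.000990) = 0.000645, standard error 2.54 points. With t on 23 df (2.07) this gives ±5.3 points.
- Three districts, t on 2 df (4.30):

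| ρ_d | Standard error (points) | Ratio to school-only | 95% half-width | Effective n |
|---|---|---|---|---|
| 0.01 | 3.66 | 1.44 | ±15.8 | 156 |
| 0.02 | 4.52 | 1.78 | ±19.4 | 103 |
| 0.05 | 6.43 | 2.53 | ±27.7 | 51 |

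The school-only effective n is 325. Much of the widening comes from the multiplier: with ρ_d = 0, 2 df alone would give ±10.9 points. The formula treats the three units as drawn with replacement. Tanzania drew three of six zones and Uganda three of four, so it overstates the between-zone part somewhat.

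**5. Where the variance can be estimated.** In Tanzania and Uganda the zones were themselves sampled. Variation between the three sampled zones carries the lower stages, on about 2 df. In Ghana the belts were not sampled and act as strata. One district per belt then gives no estimate of district variance within a belt, and the 2 df figure is only an approximation that ignores the strata.

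**The case against.** The case on the other side is substantial, and much of it stands.

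- A reader might infer that no weights or design-based variance are planned. The article does not say so. It is a condensed account, it does not name the levels of its multilevel models, and such detail may sit in an analysis plan that is not shown. Silence here is not a finding.
- A reader might infer that prevalence estimates will be biased and over-precise. That is conditional. Bias needs unweighted pooling, shares away from 50:50 and prevalence that differs between strata, all together. Over-precision needs district clustering to be ignored. No passage commits to a pooled national estimate, and prevalence in different settings is compatible with stratified reporting.
- Zones left unselected in Tanzania and Uganda are what random sampling produces. A small number of randomly drawn units costs precision and does not by itself cause bias.
- It would be wrong to say that national sampling error cannot be estimated in any of the countries. The gap is specific to Ghana.
- The article mentions no separate prevalence paper, and its stated aim is effectiveness.
- The article discloses every stage and eligibility limit, and Study setting and sampling words its claim more softly.

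None of this rescues the Discussion sentence, which is a positive claim about students and teachers. Weights cannot bring back excluded school types or unsampled grades, and they cannot add districts. Disclosure lets a careful reader discount the claim but does not make it correct.

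**Conclusion.** The point holds as a contradiction between a stated property and the stated design. The samples represent, at most, eligible public, day, mixed-gender schools and the sampled grades, observed through three districts per country.

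The consequences for estimates are conditional. An unweighted pooled figure could be off by 0 to about 8 points from the location quota, for an assumed rural share of 50% to 90% and gap of 0 to 20 points. An interval that counts only school clustering would be about ±5 points, where three districts support about ±16 to ±28, at an assumed prevalence of 70% and district intraclass correlation of 0.01 to 0.05. The article supplies none of these assumed values, so the figures show scale and are not predictions.

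The randomized comparison within school pairs is untouched: allocation, primary outcomes, power and the intention-to-treat analysis do not depend on national representativeness. The change is worth making because it is cheap and alters what the trial may conclude about prevalence.

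**What to change.** 1. In the Discussion, delete or qualify the phrase nationally representative, and bring the sentence in Study setting and sampling into line.
2. Define the target population as eligible public, day, mixed-gender schools (at most 50 teachers, small schools merged) and the sampled grades. Add the three-district limit to the limitations.
3. Report baseline prevalence by country, school type and urban/rural location. Note that in entirely urban districts such as Mwanza the rural label comes from a ward-level classification.
4. If a pooled country figure is given, use design weights built from the PPS stages, the number of listed schools per stratum and, for students, the grade size. Weights for merged schools will be approximate. Base the variance on the three first-stage units per country. State that in Ghana one district per belt leaves the within-belt district variance inestimable.

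**Cost.** Items 1 to 3 are text and tabulation. Item 4 needs some work on the school lists that the plan will obtain, and it widens intervals. As a guide, the variance inflation from weighting four equally allocated strata is 4 × ΣW². With assumed rural and primary shares of 70% each, this is 4 × (0.49² + 0.21² + 0.21² + 0.09²) = 1.35; with 80% each it is 1.85. Sampling, randomization and the treatment analysis need no change.

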## Data Availability

All study materials and the datasets generated and/or analyzed during the current study will be available from the corresponding author on request.
